**Trial registration number:**

NCT01916694; Pre-results.

Strengths and limitations of this studyThis will be the most rigorous and robust evaluation of an integrated telehealth solution for the gestational diabetes population to date.The intervention has been developed and piloted prior to the study with input from consumer groups: patients, clinicians and biomedical engineers.This study will be conducted within the maternity diabetes service of a National Health Service (NHS) hospital, therefore capturing data in a ‘real-life’ scenario.As adverse clinical outcomes such as shoulder dystocia, birth trauma or stillbirth are relatively uncommon in women with gestational diabetes mellitus receiving treatment, this study will not be able to be powered on these outcomes.The optimal metric for measuring glycaemic control in the gestational diabetic population is not known. We plan to assess the difference in overall mean blood glucose between the two groups as the primary outcome for this trial; however, an intended objective will also be to assess and compare other summative metrics of glucose control. This will enable us to select a valid primary outcome measure, with known SD and estimation of effect size, to allow calculation of sample size for a future definitive trial.The study will be conducted in a single UK tertiary centre where women have high rates of literacy and relatively low levels of social deprivation; therefore, further evaluation will be needed to demonstrate effectiveness in other settings.

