### Study design

This is an open-label, individually randomised controlled trial of 200 women who have had an abnormal oral glucose tolerance test (OGTT) in their current pregnancy. Patients are randomised to the intervention (using the GDm-health management system) and half the number of clinic visits or to normal clinic care. Patient participation is from recruitment (a time point in pregnancy between 14 and 34 completed weeks of pregnancy) until delivery.

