### Randomisation

Participants will be randomly allocated to one of two groups using a partial minimisation procedure. This will adjust the randomisation probabilities between groups to balance important covariates including gestational age at recruitment (<28 or ≥28 weeks), weight at randomisation (<90 or ≥90 kg) and ethnic group (Caucasian/white or other) using Oxford University Primary Care Clinical Trials Unit randomisation system—Sortition.^21^ This is an online randomisation programme with secure access for predesignated individuals (investigators from the trial). Randomisation will be carried out at the time of recruitment by the investigators by logging onto the system to obtain the next allocation. Women will be randomised individually into the study in an equal ratio of standard care (control) to remote monitoring (intervention). Both groups will use the same glucose meter (OneTouch UltraEasy, LifeScan, Inc).

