### Accrual and analysis

#### Sample size

The four published randomised trials that investigated the effect of a telehealth intervention on mean BG control in pregnancy reported SDs between 0.2 and 1.2 mmol/L. The lower value was from a very small study (n=19) conducted in 1996.^22^ The range of SD for mean BG in the three relatively large studies (n>30) was 0.5–1.2 mmol/L.^13^
^15^
^17^ This indicates that we do not yet have a precise estimate of the likely SD in mean BG, making sample size calculation challenging. We therefore pragmatically decided to assume an SD of 0.8 mmol/L for the mean BG level at the end point. Thus, with 100 patients in each arm, we will be able to detect a difference between the arms of 0.32 mmol/L, with power of 80% and a significance level of 0.05.

The multilevel analysis we propose has not been conducted in any of the previous studies and will use all the data from recruitment to delivery. Thus, the difference in BG between the arms at the study end point will be estimated more precisely compared with a trial that uses a comparison of mean BG at the end point alone or a mean of all readings. Therefore, the calculation given provides a conservative estimate of the effect size that could be detected.

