Gestational age at delivery (and percentage of deliveries before 37 weeks);Birth weight (and percentage of babies with birth weight above 90th centile as per the INTERGROWTH-21st Standards for gestational age and gender);Mode of delivery (vaginal, caesarean, assisted);Perineal trauma (third-degree or fourth-degree perineal tear or tear requiring suturing in the operating room);Incidence of shoulder dystocia/birth injury;Incidence of neonatal hypoglycaemia (defined as a serum BG level of <1.5 mmol/L at any time, or requiring special care baby unit (SCBU) admission for feeding);Incidence of neonatal significant hyperbilirubinaemia (defined as requiring phototherapy indicated by a serum bilirubin level of >200 μmol/L at <35 weeks, >250 μmol/L at 35–36 weeks and >300 μmol/L at ≥37 weeks);Maternal weight gain (adjusted for weeks in trial);Maternal pregnancy-induced hypertension or pre-eclampsia (defined according to the International Society for the Study of Hypertension in Pregnancy (ISSHP) criteria^23^);Admission to higher level of care for mother;Admission to higher level of care for neonate.

*Maternal and neonatal outcome analysis*: An analysis of covariance will be carried out when the outcome variable is continuous. The model will contain the term for randomisation group and baseline covariates. The results of a comparison between the two groups will be reported as a treatment effect with 95% CI. The binary variables will be analysed using logistic regression. The model will contain a term for randomisation group and baseline covariates. The results of a comparison between the two groups will be reported as an OR and a risk difference with 95% CI.

*Participants' attitudes*
Patients' attitudes will be assessed by completion of the Oxford Maternity Diabetes Satisfaction survey. This survey was developed based on several existing satisfaction surveys for diabetes management and was adapted and validated within this population.^20^ Descriptive analysis of the scores will be presented and thematic analysis of free-text comments performed.

*Compliance with the BG monitoring system*: Summary statistics will be calculated to describe the frequency of BG measurements.

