## Discussion

This trial will give valuable information regarding the role of remote BG monitoring in women with GDM. We will determine the efficacy of remote monitoring in pregnant women with GDM compared to conventional care and provide an objective assessment of the potential value of the technology in impacting outcomes including BG control, patient satisfaction and resource use. Severe adverse clinical outcomes, such as shoulder dystocia or neonatal hypoglycaemia, associated with GDM are relatively uncommon among women receiving management. Therefore, we will use a measure of glycaemic control as our primary outcome as this has been shown in large studies^3^
^4^ to correlate with risk of adverse outcomes.

Selecting a clinically relevant summary measure of glycaemic control in pregnancy is challenging owing to the progressively changing physiology of glucose regulation in the third trimester of pregnancy. We plan to assess the difference in overall mean BG between the two groups as the primary outcome for this trial; however, an intended objective will also be to assess and compare other summative metrics of glucose control including HbA1c, changes in BG over gestation and changes in BG in relation to meal times between the two groups. This will enable us to select a valid primary outcome measure, with known SD and estimation of effect size, to allow calculation of sample size for a future definitive trial.

One of the criticisms of the vast number of health-related ‘apps' now available is that there is currently little empirical evidence to support their use. Most ‘apps' have been developed by the commercial sector or by patient groups, but few are integrated within the healthcare system. We hope that the results of our trial will provide some of the first robust findings on the potential for integrated remote monitoring systems to affect patient outcomes.

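### Covariate-adjusted logistic regression is fixed for every binary outcome, including at least two the protocol calls uncommon; at event rates of about 1–3% the adjusted odds ratio may be non-estimable or very unstable

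*Protocol article*

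**What the plan says.** Under Secondary end point analysis, the paragraph on maternal and neonatal outcomes sets one method for all binary variables: "The binary variables will be analysed using logistic regression. The model will contain a term for randomisation group and baseline covariates". Each comparison is to be reported as an odds ratio and a risk difference, both with 95% confidence intervals. The covariates for these models are not named, and no event count changes the method.

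The list of outcomes just above includes shoulder dystocia/birth injury and neonatal hypoglycaemia. The Discussion says of these: "Severe adverse clinical outcomes, such as shoulder dystocia or neonatal hypoglycaemia, associated with GDM are relatively uncommon among women receiving management". The Strengths and limitations list describes shoulder dystocia, birth trauma and stillbirth in similar terms and concludes that "this study will not be able to be powered on these outcomes". Stillbirth is not among the listed outcomes.

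Study design describes an "individually randomised controlled trial of 200 women", allocated 1:1 according to Randomisation, so 100 per arm. No event rate is given for any outcome.

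**The concern.** Ordinary (maximum-likelihood) logistic regression has no finite estimate of the allocation effect when one arm has no event. If neither arm has an event, the effect is undefined. With a handful of events spread over several covariates, the fit can also fail through separation on a covariate, or converge with an interval too wide to use. The protocol commits to this model for outcomes that it expects to be uncommon in 200 women.

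The intervention halves the scheduled clinic visits, so a reader will look at these outcomes for any sign of harm. If the prescribed analysis fails there, a substitute would have to be chosen after the event counts are known.

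**Working it through.** **Inputs from the protocol article**
- 200 women, 1:1, so 100 per arm (Study design; Randomisation).
- Logistic regression with allocation and baseline covariates for all binary outcomes (Secondary end point analysis).

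**Assumptions**
- Event rate p, equal in both arms, from 1% to 10%; the article gives none.
- Four covariates, borrowed from the primary model (age, BMI, gestation at recruitment, ethnic group). With allocation this makes five parameters besides the intercept.
- No dropout, which favours the plan.

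**The plan's own figure first.** The only sample-size statement concerns the primary outcome. It takes "assume an SD of 0.8 mmol/L for the mean BG level at the end point" and says that "with 100 patients in each arm, we will be able to detect a difference between the arms of 0.32 mmol/L" can be found "with power of 80% and a significance level of 0.05". With a two-sided test, the detectable difference is 0.8 × √(2/100) × (1.960 + 0.842) = 0.317 mmol/L. This needs 99 per arm for 0.32, and power at 100 per arm is 80.7%. The figure reproduces, but it says nothing about the binary outcomes.

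**Chance of an empty arm.** One arm of 100 has no event with probability q = (1 − p)^100. At least one arm is empty with probability 1 − (1 − q)².

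| p | expected events (200p) | events per parameter (÷5) | q | P(at least one empty arm) |
|---|---|---|---|---|
| 1% | 2 | 0.4 | 0.3660 | 1 − 0.6340² = 59.8% |
| 2% | 4 | 0.8 | 0.1326 | 1 − 0.8674² = 24.8% |
| 3% | 6 | 1.2 | 0.0476 | 1 − 0.9524² = 9.3% |
| 5% | 10 | 2 | 0.0059 | 1 − 0.9941² = 1.2% |
| 10% | 20 | 4 | 0.00003 | below 0.01% |

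Both arms are empty with probability q²: 13.4% at 1% and 1.8% at 2%.

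**Unequal rates.** With a control rate of 2% and a true odds ratio of 2, the odds are 2 × 0.02/0.98 = 0.0408, so the other arm's rate is 0.0408/1.0408 = 3.92%. P(at least one empty arm) = 1 − (1 − 0.1326)(1 − 0.0183) = 14.8%. With a control rate of 1% it is 45.2%.

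**Behaviour of the adjusted model.** For each rate, 2,000 trials were simulated with allocation, three continuous covariates and one binary covariate (25% prevalence assumed), and no true effects.

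| p | at least one coefficient not estimable | median upper/lower 95% limit of the odds ratio, where the fit succeeded |
|---|---|---|
| 1% | 78% | 137 |
| 2% | 50% | 59 |
| 3% | 27% | 32 |
| 5% | 10% | 15 |
| 10% | 0.8% | 6.9 |
| 20% | 0% | 4.2 |

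The middle column includes separation on the binary covariate, which would not by itself prevent estimation of the allocation odds ratio. It is therefore an upper bound on failure of that odds ratio; the empty-arm probabilities are the firm part.

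**The risk difference survives.** Take 4 v 0 events in 100 v 100. The Wilson limits are 1.57% to 9.84% for 4/100 and 0 to 3.70% for 0/100. Newcombe's interval for the difference of 4.0 percentage points runs from 4.0 − √((4.0 − 1.57)² + 3.70²) = −0.4 to 4.0 + √((9.84 − 4.0)² + 0²) = 9.8 points. The maximum-likelihood odds ratio for the same data is infinite.

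**The case against.** The strongest reply is that a sparse-data fallback belongs in the SAP, which is not shown, so its absence here is no fault. That is right about absence. What remains is that the article positively assigns one adjusted model and an odds ratio with interval to every binary outcome, including those it expects to be uncommon.

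Second, the text says only logistic regression. It does not specify maximum likelihood or Wald intervals, and penalised or exact logistic regression would satisfy the sentence. This stands as far as it goes: the ordinary reading is maximum likelihood, and one clarifying sentence would settle it. The article also already asks for a risk difference, which stays estimable with an empty arm.

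Third, a reader might infer that several odds ratios are bound to fail. The documents do not support that. Only shoulder dystocia/birth injury and neonatal hypoglycaemia, among the listed outcomes, are called uncommon. Nothing is said about the frequency of perineal trauma, maternal or neonatal admission, hyperbilirubinaemia or hypertension. Several definitions are broad, and uncommon need not mean 1–3%. At 5% the empty-arm risk is about 1%.

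Fourth, power is disclaimed for the severe outcomes. This lowers the stakes without disposing of the point: low power gives a wide but valid interval, whereas an empty arm gives no finite odds ratio and no usable Wald interval.

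**Conclusion.** The point holds as a conditional weakness of low severity. For at least two outcomes that the protocol itself calls uncommon, the prescribed model may give no finite odds ratio, or a very unstable one, if event rates are about 1–3%. The chance of an empty arm is then about 60% to 9%. It falls to about 1% at a 5% rate and is negligible at 10%.

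The conclusion rests on assumed rates and on ordinary maximum-likelihood fitting. The simulated instability also rests on an assumed set of four covariates. These are secondary outcomes, and the primary comparison of blood glucose is unaffected. With two to six events no method will be informative about harm; the gain is a finite estimate, a valid interval and a method chosen in advance.

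**What to change.** In the paragraph on maternal and neonatal outcome analysis, add a rule triggered by sparse data: for example, fewer than a stated number of events in total, set somewhere between 10 and 20 and counted without regard to arm, or an empty arm. The empty-arm check needs only coded arm labels, so it fits the article's statement that analyses are blinded to allocation. When the rule applies:

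- take the odds ratio from Firth-penalised logistic regression with allocation and at most the three minimisation factors, with profile-likelihood limits;
- make the unadjusted risk difference with a Newcombe (score-based) 95% interval the main result.

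Keep the adjusted logistic model for the commoner outcomes. The threshold should stay low. A rule such as 10 events per parameter would mean 5 × 10 = 50 events, a 25% rate in 200 women, and would displace the adjusted model where the simulation shows it works (0.8% failures at a 10% rate, none at 20%).

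The cost is a sentence or two of text and standard software, with no new data. The downside is less covariate adjustment and slight shrinkage of the odds ratio for the sparse outcomes.

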## Methods and analysis

### Objectives

The primary objective of this trial is to evaluate the efficacy of monitoring BG in pregnancy using remote glucose monitoring (GDm-health) compared to standard clinic care. Efficacy will be determined by comparing BG control as determined by mean BG readings from recruitment until delivery between the intervention and the control group. The secondary objective will be to compare the two groups for compliance to the allocated BG monitoring regime, maternal and neonatal outcomes, glycaemic control using glycated haemoglobin (HbA1c) and other BG metrics, and patient attitudes to care assessed using a validated questionnaire^20^ and resource use.

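### Patient attitudes are to be compared between the arms, but the stated analysis of the survey is descriptive, with no between-arm estimate or interval

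*Protocol article*

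**What the plan says.** The comparison is promised in several places. The Introduction paragraph of the Abstract lists patient satisfaction among the outcomes on which the system's impact is to be tested against standard clinic care. The Objectives section says "The secondary objective will be to compare the two groups for compliance to the allocated BG monitoring regime", and the same sentence goes on to include "patient attitudes to care assessed using a validated questionnaire". The Abstract's methods paragraph repeats this objective. The Discussion expects the trial to "provide an objective assessment of the potential value of the technology in impacting outcomes including BG control, patient satisfaction and resource use".

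For the survey itself, the Secondary end point analysis section says: "Descriptive analysis of the scores will be presented and thematic analysis of free-text comments performed". It names no effect measure, interval or test, and it does not say whether the scores will be split by arm.

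For continuous maternal and neonatal outcomes the same section says: "The results of a comparison between the two groups will be reported as a treatment effect with 95% CI". Binary outcomes get an odds ratio and a risk difference, also with 95% CIs. The economic analysis is mainly descriptive, but mean cost differences with 95% CIs are added for the cost drivers it identifies.

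**The concern.** The aim and the method do not match. A comparison between randomised arms is normally answered by an estimate of the difference with its uncertainty. A description of scores does not supply that. The article separates descriptive from inferential work elsewhere and places the survey on the descriptive side, so this is a stated lesser method and more than a detail awaiting the analysis plan. An analysis plan that followed the article would contain no between-arm estimate for attitudes, and one that added it would go beyond the published plan.

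The Introduction cites improved satisfaction as one of the areas where telehealth evidence is favourable, so the trial's readers will look for a result here. They would have two sets of summaries at best, with no statement of how large a difference the data support or exclude.

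**Working it through.** **1. The sections side by side**

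| Outcome | Stated aim | Stated analysis |
|---|---|---|
| Maternal and neonatal outcomes | compare the groups | treatment effect, or odds ratio and risk difference, with 95% CI |
| HbA1c | compare the groups | mixed model; rate of change compared between groups |
| Cost drivers | compare resource use | mean cost differences with 95% CI |
| Patient attitudes | compare the groups; test impact on satisfaction | descriptive scores and thematic analysis |
| Compliance | compare the groups | summary statistics |

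Attitudes and compliance are the two items in the objective with no between-arm estimate.

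**2. The plan's own sample-size figure**

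The Study design section describes an "open-label, individually randomised controlled trial of 200 women", allocated in equal ratio. The Sample size section uses 100 per arm, SD 0.8 mmol/L, 80% power and a 0.05 level (taken as two-sided) for mean blood glucose.

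- Detectable difference = (1.960 + 0.842) × 0.8 × √(2/100) = 0.317 mmol/L, against 0.32 stated.
- n per arm for 0.32 = 2 × (2.802 × 0.8 / 0.32)² = 98.1, rounded up to 99, against 100 stated.
- Power at 100 per arm is 80.7%.

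The figure reproduces, and nothing here challenges it. No size or precision is stated for the survey.

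**3. What an interval for the survey would look like**

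The documents give neither a survey SD nor a return rate. Results are therefore in SD units of the score, over an assumed range of return, equal in both arms. Covariate adjustment is ignored.

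- 95% CI half-width = 1.960 × √(2/n)
- Difference detectable with 80% power = 2.802 × √(2/n)

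| Assumed return | Forms per arm (n) | Half-width (SD) | Detectable (SD) |
|---|---|---|---|
| 100% | 100 | 0.28 | 0.40 |
| 90% | 90 | 0.29 | 0.42 |
| 80% | 80 | 0.31 | 0.44 |
| 70% | 70 | 0.33 | 0.47 |
| 60% | 60 | 0.36 | 0.51 |

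An interval is feasible across the range. It would be informative about moderate differences and wide relative to small ones.

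**The case against.** A descriptive analysis is a legitimate choice for a secondary questionnaire, and comparing need not mean formal inference. Compliance, the first item in the same objective, is handled in the same way: "Summary statistics will be calculated to describe the frequency of BG measurements". That suggests deliberate tiering, with models for glycaemic and clinical outcomes and description for the rest. The trial is also presented as groundwork for a later definitive trial. This argument has weight, but the tiering does not fit an Abstract that speaks of testing the impact on satisfaction, and the cost analysis, itself labelled exploratory, still gets intervals. Compliance is a second instance of the mismatch and does not excuse the first.

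Three stronger readings are tempting and are not supported.

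- A reader might infer that the trial cannot say whether satisfaction differs. The survey is collected under randomisation, and if number, mean and SD are given by arm, a crude difference and interval follow by arithmetic. They would lack adjustment for the minimisation factors.
- A reader might infer that form return will differ by arm because only the intervention arm has a phone to send back. The Ethical issues section offers every participant a £20 voucher for returning equipment and questionnaires, and both arms use the same meter. No figure in the article points to differential return. Reporting return by arm is sensible, but bias from it is conjecture.
- A reader might infer that a model would protect against chance differences in the means. It would not remove sampling variation. It would only show how large that variation is.

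**Conclusion.** The mismatch stands. The article sets out to compare the arms on attitudes and to test impact on satisfaction, then names an analysis that yields neither a between-arm estimate nor an interval. The consequence is limited to one part of a secondary objective and involves no numerical error. What is lost is a reported effect with its uncertainty, which at an assumed 60% to 100% return would have had a 95% CI half-width of about 0.36 to 0.28 SD. That size rests on the assumed return and on an unadjusted comparison of means. The conclusion about the mismatch depends on neither.

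**What to change.** In the part of the Secondary end point analysis section on participants' attitudes, keep the descriptive and thematic analyses and add: the between-arm difference in the survey score or scores, as defined by the validated instrument, with a 95% CI, adjusted for the minimisation factors (gestational age at recruitment, weight and ethnic group), among all randomised women with a returned form; and the return rate by arm. The article does not say whether the instrument has a total score, so the wording should defer to the instrument's own definition.

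The cost is one sentence and one regression on data already collected. The downside is that the interval may be wide. If the authors prefer to stay descriptive, the lesser alternative is to state that attitudes will be described by arm without inference, and to soften the Abstract, Objectives and Discussion to match.

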## Abstract

**Introduction:**

The prevalence of gestational diabetes mellitus (GDM) is rising in the UK. Good glycaemic control improves maternal and neonatal outcomes. Frequent clinical review of patients with GDM by healthcare professionals is required owing to the rapidly changing physiology of pregnancy and its unpredictable course. Novel technologies that allow home blood glucose (BG) monitoring with results transmitted in real time to a healthcare professional have the potential to deliver good-quality healthcare to women more conveniently and at a lower cost to the patient and the healthcare provider compared to the conventional face-to-face or telephone-based consultation. We have developed an integrated GDm-health management system and aim to test the impact of using this system on maternal glycaemic control, costs, patient satisfaction and maternal and neonatal outcomes compared to standard clinic care in a single large publicly funded (National Health Service (NHS)) maternity unit.

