An exploratory economic investigation of the TREAT-GDM data will take the form of a detailed cost analysis from an NHS and personal perspective of the healthcare treatment pathways of pregnant women using the digital health intervention and those receiving standard clinic care. For the NHS perspective, the exploratory analysis will aim to identify cost differences between both groups in terms of healthcare resource use during delivery, neonatal care, antenatal clinics, redistribution of time for health professionals and medication and associated titration. Personal care categories will concentrate on estimating travel-related costs. A thorough cost analysis of adopting the digital health intervention at a hospital level will be reported. We will report unit costs, resource use and costs separately between treatment arms as restarted by best practice guidelines.^24^

*Economic analysis*: The statistical analysis used for the exploratory economic analysis will be primarily descriptive, and parametric inferences to detect potential statistical cost differences between arms will be conducted only on identified potential cost drivers in the exploratory analysis. For the latter, mean cost differences will be accompanied by appropriate measures of uncertainty including 95% CIs.

Interim analyses will not be performed, and all analyses will be performed after the end of the study. Analyses will be blinded to allocation group.

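### Cost intervals are confined to items picked from an exploratory look at the same data, and none is provided for net cost per woman

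*Protocol article*

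**What the plan says.** The economic text stands at the end of the protocol article's section on secondary end point analysis. It describes two linked steps.

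- **Exploratory step.** "An exploratory economic investigation of the TREAT-GDM data will take the form of a detailed cost analysis from an NHS and personal perspective". For the NHS side, "the exploratory analysis will aim to identify cost differences between both groups in terms of healthcare resource use during delivery, neonatal care, antenatal clinics", and the list continues with staff time and with medication and its titration, which makes five NHS categories. On the personal side, "Personal care categories will concentrate on estimating travel-related costs".
- **Inferential step.** "parametric inferences to detect potential statistical cost differences between arms will be conducted only on identified potential cost drivers in the exploratory analysis". The 95% CIs on mean cost differences are attached to this second step.

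The same text sets the status of the work: "The statistical analysis used for the exploratory economic analysis will be primarily descriptive". It also promises unit costs, resource use and costs by arm, and a cost analysis of adopting the system at hospital level.

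The introduction in the abstract sets a broader purpose, an "aim to test the impact of using this system on maternal glycaemic control, costs, patient satisfaction" and clinical outcomes.

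**The concern.** The second step takes its items from the first. Both use the same women, and the stated purpose of the first is to find differences between the arms. A parametric test or CI assumes that the item was fixed before the data were seen. If an item reaches the second step because its arms looked different, the usual reference distribution no longer applies and the nominal 95% no longer describes the interval.

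The rule also restricts inference to the selected items. The question that motivates the trial on costs is whether the system saves or adds money overall, and no overall cost per woman is named for comparison. That matters in this design because the intervention arm attends clinic half as often by intention. A clinic saving is close to guaranteed and would be an obvious item to select. The costs that could offset it (midwife review of remote readings, calls and messages, phone, adapter and server) may be reported without an interval. A reader would then see a precise saving and no estimate of uncertainty for the net effect.

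**Working it through.** **The plan's own figures.** No number is given for the economic analysis, so there is none to reproduce. The only design calculation is for mean blood glucose (SD 0.8 mmol/L, 100 per arm, 80% power, significance level 0.05, taken as two-sided). It reproduces: 0.8 × √(2/100) × (1.960 + 0.842) = 0.317, against 0.32 stated. It has no bearing on costs.

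**Inputs.** From the protocol: five NHS cost categories, six with travel; 100 women per arm; 95% CIs, with no allowance for selection described. Assumed, because the protocol does not give them: the selection rule, the correlation between categories (0 or 0.3) and the skewness of costs (lognormal, SD 0.83 on the log scale).

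**Reading A: drivers are chosen on the observed arm difference.** Suppose that the category with the largest standardised difference is tested and that no category truly differs. For k independent categories the chance of a nominal p<0.05 is 1 − 0.95^k.

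- k = 5: 1 − 0.7738 = 22.6%. The nominal 95% CI for the selected item then covers the true value of zero in 77.4% of trials.
- k = 6, with travel: 1 − 0.7351 = 26.5%.
- k = 3: 1 − 0.8574 = 14.3%. This drops clinics and staff time, which the intervention changes by design, and leaves delivery, neonatal care and medication as possible nulls.

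A simulation with skewed costs (20,000 trials, unequal-variance t statistic) gives similar values: 21.6% and 20.5% for five categories at correlation 0 and 0.3, and 25.9% and 23.8% for six. If the two largest differences out of five are tested, the error rate per test is about 12%.

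**Reading B: drivers are the largest cost items, pooled over arms.** In the same simulation, testing the two largest items gives an error per test of 4.7 to 4.8%. The chance of at least one false positive is 9.0 to 9.5%, close to 1 − 0.95² = 9.75%. That is ordinary multiplicity for two tests, with no selection effect.

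**What receives an interval under the rule as written, on either reading:**

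- Clinic visits (halved by design): a CI if selected.
- Staff time (remote review at least three times weekly, plus contacts): a CI if selected.
- Phone, Bluetooth adapter and server: not among the five categories. They would fall under the hospital-level cost analysis, for which no CI is stated.
- Net cost per woman: not named, so no CI is provided for.

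**The case against.** The strongest reply is that the text does not say how a driver is chosen. The term can mean an item that makes up much of the cost in either arm, and under that meaning the error per test is sound. This stands. A reader might infer that selection on the arm difference is a settled feature of the plan. It is the natural reading of a step that looks for differences and passes on what it identifies, but the protocol does not fix it.

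The 23% figure also needs care. It equals the chance of at least one nominal finding among five independent categories that were all named in advance and all tested. What selection adds is that the reader sees one nominal interval and not how many were searched. The all-null case is also unrealistic here, since clinic and staff costs should differ by design. A reader might infer that a spurious finding is likely. The figures do not support that, even at their highest.

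A reader might also infer that total cost is excluded from testing. The text does not say so. It restricts inference to identified drivers and names no total. A total could still be described, and costs by arm are promised without condition, so staff costs will not be hidden. The stated aim concerns costs in general, and the section on objectives lists only resource use; neither defines the target as a cost difference per woman. The text promises intervals and does not mention p-values.

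Finally, this is a condensed article and an analysis plan may hold the list of drivers. Missing detail would be no finding. The point here is the stated restriction: a plan that gave a CI for total cost would depart from it, unless the total were counted as a driver. Blinding the analysis to allocation does not remove the selection, because a difference between two unlabelled groups can still be seen.

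**Conclusion.** The point holds in a limited form. The protocol restricts tests and CIs to items identified in an exploratory analysis of the same data, an analysis aimed at finding arm differences, and it provides no interval for net cost per woman.

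The selection problem is conditional. If items are chosen on the observed difference, the error for the largest of five independent null categories is about 23%, falling to about 14% when only the three categories unaffected by design are null. These are illustrations that rest on an assumed rule (the single largest difference is tested) and on independence. If items are chosen by pooled cost, the error per test stays near 5%. The lack of an interval for net cost does not depend on which reading is right.

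Severity is minor to moderate. The economic work is openly exploratory and mainly descriptive, and the conclusion on blood glucose is not affected. What is at risk is how a cost saving would be read.

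**What to change.** Replace the restriction to identified drivers. Name in advance one economic comparison: the arm difference in total NHS cost per woman, including the GDm-health system and the staff time for remote review, with a 95% CI. Report all five listed NHS categories and travel cost with CIs whether or not they differ, labelled descriptive and unadjusted for multiplicity. The interval method can be left to the analysis plan.

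This does not remove multiplicity among the components. With six independent null items, at least one interval would still exclude zero in 26.5% of trials. The protection comes from having one named comparison and showing every item searched, so that the clinic saving can be read against the costs that offset it.

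The price is a change of wording, a few more table rows and less emphasis on single components. It assumes that staff-time and system costs can be attributed to each woman. The economic text implies that resources will be costed, but Box 1 lists no measures for staff time, equipment or travel, so this should be confirmed.
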